### Pneumococcal inoculation

**
*Preparation of bacterial stock and inoculation*
**

•    
**Initial preparation and transfer to MLW:** Microbiological and sequence confirmation of the purity of the inoculum will take place at LSTM and reference Public Health England laboratories prior to the onset of the study. Once complete, the microbiologically and genetically confirmed
*S. pneumoniae* capsular serotype 6B strain BHN418 will be transferred from the LSTM to MLW. Microbiological and serotype confirmation will take place at MLW upon receipt.

•    
**Preparation of bacteria for carriage studies at MLW:** LSTM will provide MLW with mid-log broth cultures of pneumococcus, frozen at -80°C in aliquots of glycerol-enriched media. Immediately prior to participant inoculation, aliquots will be thawed, washed twice, and re-suspended in sterile saline at an appropriate density for each inoculation dose. Our validated Standard Operating Procedure (SOP), based on LSTM protocols, will be used.

•    
**Confirmation of accuracy:** Following culture by the laboratory team at MLW, aliquots of the bacterium will be returned to the UK, as a quality control measure, to confirm the identity, purity and penicillin sensitivity of the isolate. These bacterial isolates will be sequenced in the UK to confirm identification.

•    
**Regulatory approval:**
*S. pneumoniae* transfer will be reported to the Malawian Pharmacy, Medicines and Poisons Board (PMPB, national regulatory authority) prior to initiation of the study. For our feasibility study, PMPB confirmed through the NHSRC that Malawi would adopt the UK Medicines and Health care products Regulatory Authority (MHRA) position that controlled human infection inoculation with pneumococcus is not an investigational medicinal product. However, the MHRA does give any challenge agent due consideration if used as part of a vaccine study (in which the vaccine is an IMP). PCV13 is an investigational medicinal product and has been approved by the Malawi Pharmacy and Medicines Regulatory Authority (PMRA: 10062020121) for this trial.

•    
**Inoculation:** Using a P200 micropipette, 0.1ml saline containing the desired dose of pneumococcus will be instilled into the nose. The participant will be seated in a semi-recumbent position. After inoculation, the participant will remain in this position for up to 15 mins. They will be given a post-inoculation advice sheet (including emergency contact details), thermometer, a course of amoxicillin and a daily symptom log to complete.

•    
**Dose escalation:** We will adopt a stepwise approach to escalating the inoculation dose, completing challenge in each dosage group before progression: 20,000 (n=40) → 80,000 (n=140) → 160,000 (n=20). We previously demonstrated successful carriage and safety at the 20,000 and 80,000 doses in our feasibility study
^
7–
9
^ and the 160,000 has been safely used in the Liverpool with no adverse events
^
12
^.

### Randomisation

Participants will be individually randomized to either PCV-13 (Prevenar) or normal (0.9%) saline vaccination prior to primary inoculation. A random number generator will be used to generate the randomization sequence and randomization occurs using block randomization with random block sizes of 6, 8 and 10 to ensure balanced vaccine allocations. An independent statistician will run the randomisation code for study group allocations and allocations will be stored on a secure electronic portal at MLW. The research team will be blinded to the vaccination group. Procedure: The study pharmacist will be fully unblinded and prepare each PCV-13 or normal saline according to the randomisation code. Individual doses will be prepared to maintain research team and participant blinding. Individual doses will be identified only by a randomisation identification number and barcode. Participants will be randomised on an electronic tablet immediately after screening is completed and they are confirmed eligible. The tablet will hold the randomisation identification number and barcode details. Subsequently, the vaccine barcode will be electronically confirmed against the participant identification number using the electronic tablet prior to administration. Unblinding will occur once microbiological reporting is completed for the final participant at visit G (14 days after primary inoculation). Participants entering the second stage (visit H) of the study will therefore be unblinded.

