**7.**    
**Re-screen and recruitment**: Participants will be invited to be re-challenged with pneumococcus. We will re-screen to ensure health and safety as detailed in Methods.

**8.**    
**Final inoculation:** Participants will be inoculated with
*S. pneumoniae* serotype 6B to the inside of each naris (as per stage four). We will use a single dose of 80,000 cfu/naris. This is the most established dose based on completed UK studies with robust colonisation data.

**9.**    
**Detection of pneumococcal carriage:** Nasal wash samples will be taken, according to a standardized protocol, at days 2, 7, and 14 days post inoculation (as per stage five). Classical microbiological culture will determine nasal colonisation with pneumococcal serotype 6B at each time point.

**Table 1. T1:** Study procedures and sampling schedule. Study visit A may occur for up to one month before study visit B. There will be a flexibility of up to 10 weeks after study visit B (1–11 weeks) to allow for staggering to inoculate a safe number of participants per week. Thereafter, the schedule will fix as per the table (e.g. if study visit D occurs at week 9, then E will be at 9, F at 10 and so on). There will be a further flexibility ± two weeks at visit H to facilitate appointment booking. There will be a tolerance of ± two working days for study visits F, G, K and L. FBC: full blood count; PBMCs: peripheral blood mononuclear cells; RNA: ribonucleic acid. *This is for immune measures (transcriptomics) and is not a genetic test. Serum will be used for serological testing; inflammatory markers; and biochemistry. Pregnancy test for female participants only.

Study Visit	A	B	C	D	E	F	G	First phase of study completed. Participants invited for second phase consent one -year post vaccination	H	I	J	K	L
Study Week		1	5	6	6	7	8		53	54	54	55	56
Day post inoculation				0	2	7	14			0	2	7	14
Consent (Written)		x							x				
Consent (Verbal)	x	x	x	x	x	x	x		x	x	x	x	x
Clinical Exam		x							x				
Vital Signs		x	x	x	x	x	x		x	x	x	x	x
Medical History		x							x				
Screen for AEs		x	x	x	x	x	x		x	x	x	x	x
Randomisation		x											
Vaccination		x											x
Inoculation				x						x			
HIV test		x	x						x				
Pregnancy test		x	x						x				
FBC (2.5ml)		x							x				
PBMCs (18ml)		x	x		x	x	x		x		x	x	x
Serum (2.5ml)		x	x		x	x	x		x		x	x	x
Blood RNA (2.5ml) *		x	x		x				x		x		
Nasosorption		x	x	x	x	x	x		x	x	x	x	x
Nasal Wash		x	x		x	x	x		x		x	x	x
Nasal cells		x	x		x	x	x		x		x	x	x

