### Duration

Recruitment of all participants and follow up will be completed within 28 months.

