### Vaccines

The vaccines will be purchased by the MLW clinical trials pharmaceutical team. The vaccines will be stored at the appropriate temperature and administered as per manufacturer’s instructions. Prevenar-13 will be purchased from Pfizer Pharmaceuticals and administered in a single dose via intramuscular injection (0.5mL supplied in a prefilled syringe). The normal (0.9%) saline will be administered as a single dose (0.5mL) by intramuscular injection. Our previous study in the UK used hepatitis A as the control vaccine
^
6
^, however this product is not licensed in Malawi such that saline was chosen for this study. The vaccines will be administered by experienced, trained health care professionals from MLW. Participants will be observed for 20–30 minutes following vaccination to ensure that they do not experience a reaction to the vaccine. If any adverse reaction occurs the volunteer will be transferred to the Queen Elizabeth Central Hospital High Dependency and Respiratory Unit (HDRU) or the Adult Emergency and Trauma Unit (if HDRU capacity is limited) and the study team informed. Immediate un-blinding will occur in the event of an adverse event requiring medical attention for which knowledge of the vaccine given will affect treatment and ongoing immediate care.

Normal saline has been chosen as a suitable control due to its long-established safety profile in vaccine trials and lack of effect on nasal colonisation/immunity. Sterile 0.9% saline vaccination is commonly used as a control for vaccine trials including in sub–Saharan Africa
^
19
^ and in a recently published COVID vaccine study
^
20
^. Sterile saline is licensed for use for dissolving drugs for IV, IM and SC injection and used commonly in clinical practice. Whilst injection with saline will not confer any benefit, participants will be offered PCV13 vaccination after unblinding and completion of the day 14 sample following final inoculation in phase 2 (week 56). PCV13 will also be offered to participants who do not take part in the second phase of the study (decline consent or ineligible after re-screening). 

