## Study status

At time of manuscript submission (20
^th^ August 2021), study recruitment has commenced with successful screening and randomisation of 40 participants. However, the study was paused due to increasing cases of SARS-CoV-2 within Malawi on the 16
^th^ June 2021.

Future amendments to the protocol will require approval by the National Health Research Ethics Committee and the Sponsors.

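### Opening the code at the last visit G does not guarantee that visit H entrants are unblinded; where it does unblind them, they choose re-challenge knowing their arm

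*Protocol article*

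**What the plan says.** The Randomisation section sets one trial-wide trigger: "Unblinding will occur once microbiological reporting is completed for the final participant at visit G". It then infers the status of everyone in phase 2: "Participants entering the second stage (visit H) of the study will therefore be unblinded".

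The calendar is set elsewhere.
- Table 1 (Study design) counts weeks from each participant's own vaccination at visit B: "Study Week 1 5 6 6 7 8 53 54 54 55 56". Visit G is week 8, visit H week 53 and visit L week 56, with two weeks' tolerance either way at visit H. It also allows later inoculation: "There will be a flexibility of up to 10 weeks after study visit B (1–11 weeks) to allow for staggering".
- Dose escalation and the safety section run the groups in sequence (40 at 20,000, then 140 at 80,000, then 20 at 160,000). Each group completes visit G before the next starts.
- Duration: "Recruitment of all participants and follow up will be completed within 28 months".

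Entry to phase 2 is voluntary and needs a new consent (Figure 2 legend). The Vaccines section places the PCV13 offer to phase 2 participants after both unblinding and the week 56 sample. For the others it gives no date: "PCV13 will also be offered to participants who do not take part in the second phase of the study". The Beneficence paragraph and Table 1 place PCV13 at visit L.

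The re-challenge serves secondary objectives 2 (PCV13 protection at 12 months) and 3 (effect of prior carriage). The Introduction relies on the control group to tell these two effects apart.

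**The concern.** One calendar date for the whole trial cannot fix the blinding status of an individual whose visit H depends on when that individual was vaccinated. With sequential dose groups, the earliest participants are those at 20,000. If enrolment runs long, they reach visit H before the code is opened and later participants reach it afterwards. Phase 2 would then be part blinded and part open, with blinding status tied to first challenge dose.

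Where the rule works as described, there is a second problem. The participant decides on re-challenge after learning the arm. The choice looks different to a saline recipient, who can be offered PCV13 with or without re-challenge, and to a PCV13 recipient, who gains no vaccine either way. If uptake or the type of person who returns differs by arm, the 12-month comparison is no longer between randomised groups, and analysis cannot fully restore that.

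**Working it through.** The plan gives no figure of its own for how many would be unblinded at visit H, so the check is calendar arithmetic on its stated inputs.

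**Inputs, in weeks after a participant's visit B (Table 1).** G = 8 − 1 = 7; H = 53 − 1 = 52 (50 to 54 with the tolerance); L = 56 − 1 = 55. With the longest stagger, inoculation is 11 weeks after B and G is 11 + 2 = 13. Duration: 28 months × (365.25/12/7) = 121.75 weeks.

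**When the inference is true.** Let W be the weeks from first to last vaccination. The last visit G is at W + 7 and the first visit H at 52. All visit H entrants are unblinded only if W + 7 ≤ 52, so W ≤ 45. The range runs from 50 − 13 = 37 to 54 − 7 = 47. At W = 45 accrual must be 200/45 = 4.4 vaccinations a week, and the trial ends after 45 + 55 = 100 weeks, about 23 months. That lies inside the 28-month limit.

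**If the full 28 months is used.** W = 121.75 − 55 = 66.75 weeks. The last visit G is at 66.75 + 7 = 73.75, so the first visit H precedes unblinding by 73.75 − 52 = 21.75 weeks. With even accrual (assumed), the share reaching visit H still blinded is 21.75/66.75 = 33%, about 65 of 200. The first 40 are vaccinated by week 0.2 × 66.75 = 13.35, so all of the 20,000 group is included.

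**Sensitivity.**

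| Case | Still blinded at visit H |
|---|---|
| W = 45 weeks | 0 |
| W = 52 weeks: (52 − 45)/52 = 13% | about 27 of 200 |
| W = 66.75 weeks | about 65 of 200 |
| Full 28 months, varying clock start, last visit L, visit H tolerance and late visit G | about 49 to 89 of 200 (25% to 45%) |
| 28 months read as covering phase 1 only | about 118 to 125 of 200 (59% to 63%) |

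The whole 20,000 group is caught once (W − 45)/W ≥ 0.20, that is W ≥ 56.25 weeks.

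**Study status.** At submission on 20 August 2021, "study recruitment has commenced with successful screening and randomisation of 40 participants", and the study had been paused since 16 June 2021. Someone vaccinated on the pause date reaches visit H about 15 June 2022. Had vaccination resumed on 20 August, 42.7 − 7 = 35.7 weeks would remain to vaccinate the other 160 with visit G done in time, or 4.5 a week. For anyone vaccinated before the pause date the margin is smaller.

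**The PCV13 offer.** On the 28-month timeline the first enrollee reaches visit L at week 55, which is 73.75 − 55 = 18.75 weeks before the code opens. The same holds for 18.75/66.75 = 28%, about 56 of 200. For them an offer at visit L (Table 1, Beneficence) and an offer after unblinding (Vaccines) fall on different dates.

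**The case against.** The strongest reply is that 28 months is an upper limit, not a schedule. A reader might infer that the unblinding rule cannot hold on the trial's own timeline. The documents do not support that: enrolment within about 45 weeks satisfies it. The pause arose during the pandemic, is reported after protocol V1.2, and comes without start or resumption dates. It shows that the margin is tight, not that the rule was infeasible when written. This stands.

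A reader might also infer that entry to phase 2 depends on arm by rule. It does not. Both arms are invited, and saline recipients are offered PCV13 whether they enter or decline. Entrants receive the offer about three weeks after visit H (week 56 against 53), and decliners have no stated date. Differential entry is therefore a risk of unknown size.

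Nor does the protocol say that laboratory readers will know the arm. Culture with standard confirmatory tests, checked by PCR, leaves limited room for reader bias.

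Holding the blind longer could itself do harm. Opening each code at the participant's own visit L would release about 56 of 200 allocations before the last visit G on the 28-month timeline. Holding every code until the last visit L would keep the first enrollee waiting until about week 122 rather than about week 74. Both objections are sound and shape the fix.

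Finally, phase 2 is separately consented, analysed separately and serves secondary objectives, and its open status is declared. That limits the severity but does not make the stated inference correct or protect the comparison.

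**Conclusion.** The point holds with limited scope. The inference in the Randomisation section is invalid as written; it is true for everyone only if enrolment spans about 45 weeks or less (range about 37 to 47). If the full 28 months is used with even accrual, neither of which the protocol states, about a third of participants enter phase 2 blinded and the rest unblinded, split by enrolment order and so by first challenge dose. Where unblinding comes first, voluntary consent given with knowledge of the arm creates a risk of differential entry. That weakens the between-arm comparison behind secondary objectives 2 and 3. The protocol gives no basis for putting a number on this bias. The phase 1 primary endpoint is limited to the initial challenge and stays blinded under the current rule.

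**What to change.** Reconcile Table 1, Duration, Randomisation, Vaccines and the Beneficence paragraph on when codes open and when PCV13 is offered. Which offer date applies is for the sponsor to settle.

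Replace the unblinding rule. Each participant, and the staff handling that participant's samples, stay blinded until the later of:
- (a) that participant's visit L microbiology report, or the recorded refusal or ineligibility at phase 2 re-screening; and
- (b) the last participant's visit G report.

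An unblinded statistician can analyse phase 1 once the last visit G is reported and release arm-level results only. Emergency unblinding stays as it is.

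This opens no code before phase 1 is complete. It delays no PCV13 offer beyond what the Vaccines section already implies, since that section puts the offer after unblinding and week 56. The one possible lag is laboratory turnaround on the visit L culture, which the article does not give. If it matters, the participant's code could be released once the visit L sample is taken, with the laboratory kept blinded until it reports.

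The cost is revised protocol and consent wording, and individual allocations held longer: for the last enrollee, up to 55 − 7 = 48 weeks beyond the last visit G.

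If the blind is not extended, describe phase 2 as open-label or mixed, report phase 2 uptake by arm and results by blinding status at visit H, and state that the 12-month comparison is subject to selection.

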### Vaccines

The vaccines will be purchased by the MLW clinical trials pharmaceutical team. The vaccines will be stored at the appropriate temperature and administered as per manufacturer’s instructions. Prevenar-13 will be purchased from Pfizer Pharmaceuticals and administered in a single dose via intramuscular injection (0.5mL supplied in a prefilled syringe). The normal (0.9%) saline will be administered as a single dose (0.5mL) by intramuscular injection. Our previous study in the UK used hepatitis A as the control vaccine
^
6
^, however this product is not licensed in Malawi such that saline was chosen for this study. The vaccines will be administered by experienced, trained health care professionals from MLW. Participants will be observed for 20–30 minutes following vaccination to ensure that they do not experience a reaction to the vaccine. If any adverse reaction occurs the volunteer will be transferred to the Queen Elizabeth Central Hospital High Dependency and Respiratory Unit (HDRU) or the Adult Emergency and Trauma Unit (if HDRU capacity is limited) and the study team informed. Immediate un-blinding will occur in the event of an adverse event requiring medical attention for which knowledge of the vaccine given will affect treatment and ongoing immediate care.

Normal saline has been chosen as a suitable control due to its long-established safety profile in vaccine trials and lack of effect on nasal colonisation/immunity. Sterile 0.9% saline vaccination is commonly used as a control for vaccine trials including in sub–Saharan Africa
^
19
^ and in a recently published COVID vaccine study
^
20
^. Sterile saline is licensed for use for dissolving drugs for IV, IM and SC injection and used commonly in clinical practice. Whilst injection with saline will not confer any benefit, participants will be offered PCV13 vaccination after unblinding and completion of the day 14 sample following final inoculation in phase 2 (week 56). PCV13 will also be offered to participants who do not take part in the second phase of the study (decline consent or ineligible after re-screening). 

### Determination of colonisation

Colonisation will be defined by the microbiology result of nasal washes taken at 2-, 7- and 14-days post inoculation. Nasal washes will be plated on to culture media and incubated overnight at 37°C in 5% carbon dioxide (CO
_2_). Colonies will be confirmed as
*S. pneumoniae* using classical microbiological techniques including (i) typical draughtsman-like colony morphology, (ii) the presence of α-haemolysis, (iii) optochin sensitivity and (iv) bile solubility. Typing by latex agglutination will be done using a commercial kit to confirm pneumococcal serogroup. Isolates will be frozen at -80
^o^C for storage. Results from the cultured nasal wash will also be confirmed using PCR based methods of bacterial detection.

Monitoring of colonisation will be performed by microbiology analysis of nasal washes. This will include measurement of pneumococcal density by LytA PCR. Monitoring for COVID-19 co-infection will be performed by RT-qPCR analysis of throat swab samples

### Safety during colonisation

A three-day course of amoxicillin and a digital thermometer will be given on the day of inoculation. These will be carried by the participants for immediate treatment after phone consultation should the participant develop moderate or severe symptoms as described on the participant safety advice leaflet. Participants will be required to make text message/phone contact with a specified member of the research team before 1200 hrs every day for 7 days post-inoculation
*regardless of whether they have symptoms or not*. Should they not make contact by the specified time, a member of the research team will contact the participant. If no contact is made, then a ‘secondary contact’ (established during screening visit) will be telephoned. During the post-inoculation period, participants will have access to a 24/7 on-call telephone service until the end of each phase (H and L) of the study.

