^. No episodes of pneumococcal infection or serious unexpected serious adverse reactions (SUSARS) have occurred in any of our participants whether they had no carriage, natural carriage or experimental carriage.

**
*Vaccine safety.*
** Prevenar-13 is a safe vaccine with a very low risk of adverse events
^
29,
30
^. It is currently licensed for use in children and in Malawi as part of the Childhood Immunisation programme (effective from 2011). In adults over 50 years of age vaccinated in US clinical trials the most commonly reported side effects to Prevenar-13 vaccination included: injection site pain/swelling/tenderness, fatigue, headache, muscle pain, limitation of arms movement, decreased appetite, chills and rash.

Normal (0.9%) saline is commonly used for control vaccination in vaccine efficacy trials. Normal saline is licensed for IV, IM and SC injection and is safe with minimal side effects
^
20
^.

Participants will be observed by trained research staff in the research clinic rooms after vaccination for a period of 20–30 minutes. This procedure is to mitigate the very low risk of any immediate drug reaction. The 3A research clinic rooms are situated directly opposite to a respiratory high dependency unit at Queen Elizabeth Central Hospital. In the unlikely event that a participant became unwell after vaccination, they would be transported to this ward for treatment and close monitoring.

**
*Participant safety procedures.*
** We will provide all participants with a safety information sheet
^
31
^. This sheet classifies symptoms into mild, moderate and severe. We will take a proactive approach for participants, with daily contact up until day seven post inoculation and enquiry about development of any symptoms. We will also encourage participants to report development of any symptoms with 24-hour medical cover throughout the study visit schedule. In the event of illness, we will apply standardised operating safety procedures for participants. The research team will pay for any costs associated with these procedures and participants will incur no out of pocket expenses.

**
*Mild illness.*

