** Mild illness is defined as development of any new symptom that is of concern to the participant during the study period. These may include mild coryzal symptoms such as blocked or runny nose. Participants will be encouraged to contact the research team by telephone within office hours. During the telephone assessment participants will be screened for potentially concerning moderate and severe symptoms. If there is any concern, participants will be invited to the research clinic for a detailed clinical assessment by one of the study doctors. The assessment will be fully documented within study records including rationale for any treatments and/or required modifications to study procedures.

**
*Moderate Illness.*
** Moderate illness events are defined as fever with temperature >37.5°C, shivering, headache, new rash, drowsiness, cough, new earache and or new eye infection. Participants will be clearly instructed to call the research team at any time of the day upon development of any of these symptoms. During the telephone assessment participants will be screened for severe symptoms and requested to attend either the research clinic (office hours) or Mwaiwathu hospital (outside of office hours) for medical assessment. If severe symptoms are identified on telephone assessment, participants will be asked to take antibiotics from their supplied emergency pack and attend Mwaiwathu hospital. Study doctors will assess the participants at either the research clinic or Mwaiwathu and offer appropriate treatments. The assessment will be fully documented within study records including rationale for any treatments.

**
*Severe illness.*

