** Severe illness events are defined as any symptoms that cause serious concern to participants following inoculation. We have purposefully taken a conservative approach to encourage participants to seek early medical advice and treatment if they are concerned. Participants will be counselled as to what symptoms the study team may be particularly concerned about during the consent process. These would include any potential symptoms of sepsis. In the event of severe illness, participants are requested to start taking the provided emergency antibiotics, directly attend Mwaiwathu hospital and contact the study team. A study doctor will attend the patient in Mwaiwathu and offer appropriate investigations (may include blood culture if clinically indicated) treatments. The assessment will be fully documented within study records including rationale for any treatments.

**
*COVID-19 specific participant safety procedures.*
** Participants who screen positive for COVID-19 will be excluded from the study. The study team will offer standardised advice to such participants including self-isolation measures to reduce onward transmission in line with Malawi Ministry of Health guidance
^
32
^. After an initial negative test, we will continue to screen participants for development of COVID-19 after pneumococcal inoculation at visits 4, 6 and 7. No additional samples will be required, we will use throat swabs to test for COVID-19 using RT-qPCR in line with CDC guidance
^
33
^. Participants will be notified if they become positive for COVID-19 during the study and excluded from further visits. This procedure is to facilitate self-isolation in line with guidance and to reduce the risk of transmission. If the participant has concurrent pneumococcal carriage, they will be advised to commence antibiotics to reduce the theoretical risk of bacterial co-infection. We will replace participants who are excluded during post-inoculation follow up to recruit the pre-specified allocated number of patients to each group.

**
*Evaluation of adverse events and serious adverse events*
**

**Adverse events:** Non-serious adverse events (AEs) will be collected systematically during the research and recorded in the case report form. Participants will keep a log of symptoms and this will be summarised and reported to the Data, Safety and Monitoring Board (DSMB). 

**Serious adverse events:** Any
*serious (*AE

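### The protocol places a phone consultation before the carried amoxicillin in one section, but has severely ill participants start it without a prior call in another

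*Protocol article*

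**What the plan says.** Three places in the protocol article say when the carried three-day course of amoxicillin is to be used.

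- **Safety during colonisation.** The pack is "for immediate treatment after phone consultation should the participant develop moderate or severe symptoms". The same sentence refers to the participant safety leaflet for the description of symptoms.
- **Safety considerations and assessment, moderate illness.** Moderate illness is fever above 37.5°C, or "shivering, headache, new rash, drowsiness, cough, new earache and or new eye infection". The first step in each case is a phone call: "Participants will be clearly instructed to call the research team at any time of the day upon development of any of these symptoms". The call checks for anything severe, and callers are then "requested to attend either the research clinic (office hours) or Mwaiwathu hospital (outside of office hours) for medical assessment". The pack appears once: "If severe symptoms are identified on telephone assessment, participants will be asked to take antibiotics from their supplied emergency pack and attend Mwaiwathu hospital". For the rest, "Study doctors will assess the participants at either the research clinic or Mwaiwathu and offer appropriate treatments".
- **Safety considerations and assessment, severe illness.** Severe illness is whatever seriously concerns the participant after inoculation. In that event "participants are requested to start taking the provided emergency antibiotics, directly attend Mwaiwathu hospital and contact the study team".

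The paragraph on participant safety procedures adds, of the participants' information sheet, "This sheet classifies symptoms into mild, moderate and severe". The sheet itself is not among the documents.

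**The concern.** The sentence in Safety during colonisation fixes two things: the indication for the pack (moderate or severe symptoms) and the order of events (consultation, then treatment). The two later paragraphs describe the same decision and differ from it on both.

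The order matters more. This is a challenge trial in healthy volunteers, and the carried amoxicillin is their rescue treatment. The severe-illness paragraph is deliberately conservative: it wants participants to seek help and start treatment early, and it mentions possible sepsis. A participant or staff member working from Safety during colonisation could instead expect a phone conversation before the first dose. Because severe illness is defined by the participant's own concern, participants grade themselves and need one clear instruction.

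The indication matters less. From the first sentence, staff could take a moderate symptom as enough to advise the pack by phone, when the moderate-illness paragraph wants that person examined.

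**Working it through.** There is no figure to reproduce and no calculation applies. The check is a comparison of the current text, by grade of symptom.

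| | Safety during colonisation | Safety considerations and assessment |
|---|---|---|
| **Severe: order** | Phone consultation, then treatment | Start the pack, go directly to hospital, contact the team; no call required first |
| **Moderate: indication** | Moderate symptoms named as an indication, after a call | Call, phone screen for severe symptoms, in-person assessment; pack on phone instruction only if severe symptoms are found |

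*Severe illness.* The first section makes treatment follow the consultation. The severe-illness paragraph lists three actions with contact last, and does not make it a condition of the first dose. One rule has a precondition that the other lacks, and nothing says which section governs.

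The moderate-illness paragraph does contain a route that agrees with the first section: someone who phones with moderate symptoms and is found to be severe is told to take the pack. That route covers only people who have already called. It does not cover someone who judges themselves severely ill from the start, who is the person the severe-illness paragraph addresses.

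*Moderate illness.* Both rules begin with a call. If the consultation is read as deciding whether to treat, the moderate-illness paragraph simply describes that consultation: pack if severe, otherwise attend and be assessed. Nothing in it forbids a study doctor from using amoxicillin after the assessment. What remains is that the first section names moderate symptoms as an indication in their own right and speaks of immediate treatment, which the later paragraph does not do by phone for moderate symptoms alone. This is an ambiguity of wording.

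*Could other text settle it?* The list of safety measures under Study design to ensure safety says only that the tablets are for emergencies; it sets no order and no grade. The leaflet might settle it, but it is not shown, so which instruction participants receive cannot be checked.

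**The case against.** The strongest reply is that a short general sentence is being set against later and more specific text. Safety during colonisation explains why the pack is carried, and the two later paragraphs give the procedure. The instruction that participants follow is the leaflet, supported by standard operating procedures that an article condenses. There are also strong safeguards: three nights' accommodation after challenge or twice-daily checks in its place, daily contact to day 7, a 24-hour phone line, and counselling on severe symptoms at consent. The feasibility study reported no adverse events and minimal symptoms.

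Much of this stands. It makes harm unlikely and keeps the point minor. It does not remove the difference in order for severe illness, because a more specific paragraph that drops a precondition changes the general rule. A protocol that states both orders also gives no clear standard against which to check the leaflet.

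Three stronger readings are tempting, and the documents do not support them.

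- *A reader might infer that the two rules cannot both be followed.* They can. A severely ill participant who phones, takes the tablets and goes to hospital satisfies both, since the severe-illness paragraph does not forbid calling first. For moderate illness, a consultation that decides treatment fits both texts.
- *A reader might count every symptom on the moderate list as a trigger for the pack under one section and none under the other.* Safety during colonisation takes its description of symptoms from the leaflet. Whether the leaflet's moderate group matches the list in the moderate-illness paragraph is unknown, so the count has no firm basis.
- *A reader might infer that the wording biases the carriage results*, because the strain is penicillin-sensitive and a three-day amoxicillin course is the protocol's own way of ending carriage. The documents give no rate of use from which to size an effect. The primary endpoint counts a positive wash at any time point, so a participant already positive on day 2 stays positive. The correction below would keep amoxicillin at a doctor's discretion, so it would not remove such exposure.

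**Conclusion.** The point holds as a minor inconsistency, on participant-safety grounds only. For severe illness, Safety during colonisation puts a consultation before the carried amoxicillin, while the severe-illness paragraph has participants start it with no prior call. For moderate illness there is a lesser ambiguity about whether moderate symptoms alone justify the pack, and it can largely be reconciled by reading the call as the step that decides treatment.

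No size can be given: the documents do not say how many participants would meet either situation. Nothing in the sample size, power or analysis plan changes.

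The conclusion assumes that both sections are meant to bind staff and participants as written. If the leaflet already carries the severe-illness rule, the practical risk is smaller, but the protocol sentence should still be brought into line with it.

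**What to change.** Rewrite the sentence in Safety during colonisation to match the protocol's own more specific paragraphs:

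- **Severe symptoms:** start the pack at once, attend hospital and contact the team, without waiting for a call.
- **Moderate symptoms:** call and attend for assessment; use the pack only if the call identifies severe symptoms or a study doctor decides so.

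Then check that the participant safety leaflet says the same. The cost is one sentence and one document check, handled through the usual approval of amendments. No visit, sample or analysis changes.
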